### Plans for dissemination and publication of project outcomes

After approval by the coordinating principal investigator, sub-investigators, and statistician, results of the study will be published in peer-reviewed scientific journals and presented at scientific conferences and to lay audiences where applicable. Results will be published after termination of the study. The order of authors will be at the discretion of the coordinating investigators. Factors that the coordinating investigator may take into consideration are the following: securing funding for the study, participation in organising the study, participation in meetings and the on-going development of the study, manuscript preparation, and general involvement in the study.

### Project closure processes

At the conclusion of the project, arrangements shall be made for retention of all data relating to the project (including raw and electronic data, and PICFs); this will be retained for at least 15 years following the closure of the database. With participant consent, biological products will be retained for up to 15 years, and contact details will be kept on record so that participants can be contacted again for participation in future research.

### Plans for sharing and/or future use of data and/or follow-up research

This project is inter-departmental and interdisciplinary. Data will be shared between the respective groups involved in its execution. There are plans for future use of the data and product developed in this project. If this project proves to be feasible, our group intends to use the same or similar enema FMT product and protocol and test its efficacy in a larger randomised controlled trial powered to detect changes in depressive symptomatology.

## Discussion

Despite the promising body of evidence and biological rationale to support the efficacy of FMT in MDD, the known relationship between intestinal dysbiosis and MDD [7, 23, 66–68], and the established efficacy of FMT in altering intestinal microbiota [69–71], there have been no published studies to date examining the impact of FMT on MDD in humans. FMT may represent a safe, fast, and effective way of treating MDD. This is potentially highly significant given the enormous psychosocial and economic burden of depression, and the limitations of existing treatment options. These factors provide compelling support for investigating the use of FMT in MDD.

As described above, substantial phase I evidence already exists for the safety of FMT across a broad range of indications [29], including immune-compromised populations [49] and in the long term [51]. This study is the first randomized, triple-blind, placebo-controlled feasibility trial assessing the feasibility, tolerability, and acceptability of FMT in the treatment of MDD in adults.

The present study has a long follow-up period (6 months), allowing for longer-term safety data and monitoring. The results of the present study will have multiple applications. Firstly, if the study is found to be feasible, they will be used to support and inform a fully powered efficacy study, which will also utilise a randomised, triple-blind, placebo-controlled design. Secondly, the study will allow us to determine whether enema-delivered FMT is acceptable to people with depression; this is important given the nature of this intervention, with the requirement to attend a clinic on four consecutive days to receive an intervention. Thirdly, assessing changes in gut microbiota and the degree to which any gut microbiota changes are concordant with the donor microbiota may yield useful information regarding dosing and frequency. Moreover, examination of possible biomarker changes that are linked to MDD, and in many cases the gut microbiota, may yield insights into mechanistic processes prompted by FMT. Fourth, although not powered to detect efficacy endpoints, some initial suggestions of potential changes in symptomatology and measures of well-being and functioning may be useful in understanding the sample size required for a scaled RCT. Finally, collecting and analysing initial cost-efficacy data will also inform the next steps in the application of this intervention in a clinical setting.

Choice of enema as a delivery route was based upon numerous factors, including feasibility, resource utilisation, safety, tolerability, patient preference, and efficacy. The most poorly tolerated and highest risk deliveries of FMT are via colonoscopy or nasogastric/nasoduodenal delivery [28]. Nasogastric/nasoduodenal delivery methods carry small but non-zero risks of perforation, aspiration, and vomiting, and are technically more complex to perform. Whilst considered the most efficacious, the colonoscopic route is also complex to perform in a research setting; this process requires a gastroenterologist, is more resource intensive, invasive, and has theoretical risks associated with use of sedation, bowel preparation and a risk of perforation, notwithstanding limitations in translation and dissemination [72]. On the other hand, whilst encapsulated FMT is considered a safe and efficacious route [73, 74], this product is not yet widely available in Australia.

Enema delivery is a widely used route of administration for FMT. It has several advantages including availability, safety, tolerability, and efficacy [72]. Additionally, FMT via enema does not require clinician-specific expertise to administer, is more affordable, and generally considered a more feasible option for delivery [72]. FMT via enema has been demonstrated to be efficacious at restoring gut microbiota following disruption by antibiotics [75]. Moreover, it has been shown to be safe and efficacious in the long term [76], and even in higher risk populations such as children [50]. Therefore, in balancing these many considerations, we have chosen FMT via enema as the route of administration for our current study.

The primary limitation of this study is the small sample size, meaning that the study will not be powered to statistically measure any of the intended secondary outcomes, and for this reason these are considered exploratory outcomes rather than secondary outcomes. However, the primary aim of the program is to explore feasibility, which the study has been designed to evaluate. If found to be feasible, a full-scale RCT is planned which would be adequately powered to evaluate efficacy as a primary outcome and will be powered to evaluate the secondary and exploratory outcomes of this feasibility study.

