### Procedure

Participants will receive either four active or four placebo FMT delivered via an enema will be administered over four consecutive days to each participant by a research nurse. Assessments will be conducted at baseline, and then every 2-weeks until the primary end point (8 weeks). A further follow-up assessment will then occur at week 26 to capture long-term safety data. An outline of the study schedule is provided in Table 1 and the appointment schedule is summarised in Fig. 1. Participants, investigators, assessors, and study statisticians will be blinded to group allocation. This protocol is reported as per the Standard Protocol Items: Recommended for Intervention Trials (SPIRIT) guidelines [58], and the CONSORT extension for pilot and feasibility trials checklist [59]. All study procedures will be concordant with Good Clinical Practice (GCP) principles. The consent procedure is described below under the heading Consent and Enrolment.

**Table 1 Tab1:** Schedule of assessments, instruments, and procedures to be implemented at each study appointment

Variable	Instrument	*Week (first row)* Appointment number (second row)										
		*− 2*		*0 (baseline)*				*2*	*4*	*6*	*8*	*26*
		1a	1b	2	3	4	5	6	7	8	9	10
Screening (via Telehealth)												
Enrolment	Informed consent	✓										
General inclusion criteria	Eligibility screener for entrance criteria	✓										
Alcohol and substance abuse	Alcohol Use Disorders Identification Test (AUDIT) Drug Abuse Screening Test (DAST-10)	✓										
Diagnosis of MDD	Structured Clinical Interview for the DSMI-V (SCID-V) mood disorders module		✓									
Depression severity and suicidality	Montgomery-Asberg Depression Rating Scale (MADRS)		✓									
Study appointments												
Group allocation	Randomisation spreadsheet			✓								
FMT	Enema-delivery of intervention or placebo			✓	✓	✓	✓					
Demographics	General questionnaire			✓								
Medical history	Medical history Standard psychiatric assessment Family history		✓ (optional)	✓								
Study appointments continued.												
Medication use	Current medications Medication history		✓	✓								
Personality disorders	Personality disorders (SAPAS)			✓								
Diet	Diet (Simple Dietary Questionnaire)			✓							✓	
Psychological symptoms	Depression, Anxiety and Stress symptomatology (DASS) Depression severity (MADRS) Suicidality (MADRS)			✓				✓	✓	✓	✓	
Gut symptoms	Gastrointestinal Symptom Rating Scale (GSRS)			✓				✓	✓	✓	✓	

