Medical variables	Change in medications, vaccines, illness, etc			✓				✓	✓	✓	✓	
General health and functioning	Patient Global Impression of Change Sheehan Disability Scale Sleep (Pittsburgh Sleep Quality Index) Quality of Life			✓				✓	✓	✓	✓	
Study appointments continued.												
Changes of circumstance	Medication changes questionnaire			✓				✓	✓	✓	✓	
Cost analysis	Resource Utilisation Questionnaire			✓							✓	
Physical examination	Height (stadiometer) Weight (scales) Blood pressure (sphygmomanometer) Heart rate (sphygmomanometer)			✓				✓			✓	
Blood samples	Whole blood by research nurse/ACL			✓				✓			✓	
Stool samples	Microba stool collection kits			✓				✓			✓	
Feasibility data												
Tolerability	Adverse events			✓	✓	✓	✓	✓	✓	✓	✓	✓
Adequacy of blinding	Participant questionnaire							✓				
Adherence	Monitoring questionnaire completion and appointment attendance throughout the study period			✓	✓	✓	✓	✓	✓	✓	✓	
Acceptability	Study Participant Feedback Questionnaire Specific questions pertaining to study intervention			✓				✓			✓	
Researcher/trial feasibility data												
Recruitment	Monitoring of recruitment rates by study staff throughout trial period			✓	✓	✓	✓	✓	✓	✓	✓	
Retention	Monitoring of trial attrition by study staff throughout trial period			✓	✓	✓	✓	✓	✓	✓	✓	

The study schedule allows for flexibility for all or parts of each appointment to be conducted by telehealth if this is preferable to the participant or required for other reasons

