### Primary outcome measures

The primary outcomes for this study are (1) the feasibility and (2) safety of FMT as an adjunctive treatment for MDD in adults. The study outcomes, participant appointment schedule, and study timeline are outlined in Table 1 and Fig. 1.

Feasibility will be considered as a composite outcome, measured by the following:The ability to meet recruitment targets (measured by recruitment logs, comparing actual recruitment against projected targets)Participant retention and completion rates (measured by attrition rates and completeness of data)Adherence to intended protocol (measured by completion of intervention as planned, missed appointments, technical difficulties arising, and completeness of study data)Participant acceptability (measured using the TransCelerate Study Participant Feedback Questionnaire, plus the addition of questions designed specifically for this study)Robustness of study methodology, including effectiveness of blinding (measured qualitatively based on feedback from researchers throughout and at the conclusion of the study, and a participant and researcher survey to assess blinding)

Safety of FMT as an adjunctive treatment in adults will be measured by an assessment of adverse events. These data will be collected through direct observations by the study nurse during administration of the intervention, and via participant reporting during the intervention and each appointment thereafter (measured at weeks 0, 2, 4, 6, 8, and 26). Participants will also be encouraged to contact the research team at any time to report adverse events outside of study appointments.

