
### Feasibility targets

Table 4 outlines pre-specified targets identified by the research team as a minimum standard that would indicate that the study design was feasible. These targets will also assist the study team to identify aspects of the trial that may need to be amended to improve future, large-scale trials.

**Table 4 Tab4:** Feasibility targets

Target area	Feasibility target
Recruitment	Successful enrolment of *n* = 15 participants across a 6-month active recruitment period
Retention	A minimum of *n* = 10 participants to complete study until the 8-week primary endpoint (i.e. a 33% attrition rate).
Adherence to protocol	Participants should: 1) Receive two of the total four enemas 2) Attend their baseline, week 2 and week 8 appointments 3) Provide baseline and week 2 stool samples
Safety	Nil severe and/or serious adverse events rated as likely due to study intervention in the active FMT group.
Adequacy of blinding	The best achievable outcome for adequacy blinding is participants and researchers correctly guessing allocation at a rate of 50% (the rate due to chance). Whilst we are not likely to be statistically powered to measure this outcome, we aim to reach an outcome approaching 50%.

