## Ethical, regulatory, and dissemination aspects

### Consent and enrolment

Following primary expression of interest, via any of the above listed recruitment pathways, eligible participants will be directed to the study webpage for more details, where they will be able to register an expression of interest to be contacted by a member of the study team. Potentially eligible participants will be provided with a PICF. They will also be asked to nominate a time for a member of the research team to call them to discuss the study further and book in an initial study appointment. Participants will be given the option of signing the PICF with a member of the research team either in-person or via telehealth. Signed consent must be provided prior to study enrolment.

Consent will also be obtained from participant to send reminder texts prior to appointments.

Should participants have any conditions or commitments that preclude them from participating immediately, participants will be asked to nominate their preferred starting date within the trial period. Consent will be obtained to send participants reminders via email and phone.

Consent will be confirmed again at the initial screening appointment. Participants will be made aware that they can withdraw consent (primary or extended) at any point

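### Acceptability is asked only of people who have already agreed to an enema trial, so the conclusion about people with depression in general is too broad

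*Protocol article*

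**What the plan says.** **Measure.** In the protocol article, Primary outcome measures lists five components of feasibility. One is "Participant acceptability (measured using the TransCelerate Study Participant Feedback Questionnaire, plus the addition of questions designed specifically for this study"). The matching row of Table 1 (Procedure) reads "Study Participant Feedback Questionnaire Specific questions pertaining to study intervention" and is ticked at appointments 2, 6 and 9 (weeks 0, 2 and 8). It has no tick at 1a or 1b. Table 4 sets no target for acceptability, and Feasibility analysis plans a qualitative synthesis.

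**What happens before appointment 2.** Under Consent and enrolment, "Potentially eligible participants will be provided with a PICF", followed by a call with the research team. Table 1 puts consent and the first screening items at 1a, and the SCID and MADRS at 1b. Allocation and the first enema are at appointment 2.

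**Claim.** The Discussion states that "the study will allow us to determine whether enema-delivered FMT is acceptable to people with depression". It gives the nature of the intervention and the four days of clinic attendance as the reason this matters.

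**Recruitment.** This component is "measured by recruitment logs, comparing actual recruitment against projected targets". Its Table 1 row is "Monitoring of recruitment rates by study staff throughout trial period". The Table 4 target is successful enrolment of 15 "participants across a 6-month active recruitment period". Table 1 has a row named Enrolment whose instrument is "Informed consent", ticked at 1a.

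**The concern.** The people who answer the questionnaire are selected for willingness on the very feature being rated. Someone who finds an enema, or four clinic days in a row, unacceptable can leave after reading the consent form or after the call. That person never reaches a form on which to say so. The Discussion gives the route and the attendance as the reason for asking, yet the measure is blind to the stage at which they are most likely to deter people.

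This affects a decision. Under Plans for sharing and/or future use of data, a feasible result leads to a larger randomised trial with the same or a similar enema product and protocol. That trial must be filled from the people approached. Its planners need to know what share of them will accept the route, as well as how those who accepted it felt afterwards.

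A smaller matter is the word enrolment. The Table 4 recruitment target depends on it, and the article does not use it consistently.

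**Working it through.** **1. The plan's own figures.** Study design gives 10 + 5 = 15, a ratio of 10/5 = 2. Table 4 gives 10 completers of 15, so attrition is (15 − 10)/15 = 33.3%. Both reproduce. There is no power calculation to check.

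**2. Who can answer the acceptability questionnaire.**

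| Step | Place in the article | Can a person leave over the route? | Acceptability questionnaire? |
|---|---|---|---|
| Expression of interest, consent form, call | Consent and enrolment | Yes | No |
| Consent, screening (1a, 1b) | Table 1 | Yes | No |
| Appointment 2 (allocation, first enema) | Table 1 | Yes, by refusing a dose | Yes |
| Appointments 3 to 5 (remaining enemas) | Table 1 | Yes, by refusing a dose | No |
| Weeks 2 and 8 (appointments 6 and 9) | Table 1 | Dosing is over | Yes |

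This assumes that the consent form, which is not shown, describes the enemas. On that assumption every respondent has already agreed in principle.

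**3. What a perfect result would support.** If all n respondents found the procedure acceptable, the exact one-sided 97.5% lower bound is 0.025^(1/n).
- n = 15: 0.025^(1/15) = 0.782, or 78%.
- n = 10 (active arm only): 0.025^(1/10) = 0.692, or 69%.

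Both bounds apply to consenters. Neither says anything about the people approached.

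**4. Uptake that the questionnaire cannot distinguish.** The article gives no uptake, so u is assumed. The number approached for 15 participants is 15/u:

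| Assumed uptake | 75% | 50% | 25% | 10% |
|---|---|---|---|---|
| Approached | 20 | 30 | 60 | 150 |

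**5. How far the two populations could differ.** Assume that 13 of 15 participants rate the procedure acceptable (13/15 = 87%) and that d further people decline because of the route. The share acceptable among consenters and route-decliners together is 13/(15 + d):

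| Assumed d | 0 | 5 | 10 | 20 |
|---|---|---|---|---|
| 13/(15 + d) | 87% | 65% | 52% | 37% |

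All inputs here are assumed. The plan neither sets nor schedules an acceptability percentage.

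**6. The word enrolment.** The relevant places are:
- Table 1 equates enrolment with consent at 1a.
- Consent and enrolment puts signed consent before enrolment.
- Study population describes the 15 as people with confirmed MDD and a MADRS of at least 20, and the Table 2 caption ties the enrolled to the eligibility criteria.
- Study design makes the 15 equal to 10 + 5 allocated.
- Safety requirements links the number issued at enrolment to the allocated intervention.

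If the Table 1 label were applied to Table 4 and a share s of consenters failed screening (assumed), then:

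| Assumed s | 10% | 20% | 30% | 50% |
|---|---|---|---|---|
| Randomised from 15 consents, 15(1 − s) | 13.5 | 12 | 10.5 | 7.5 |
| Consents needed for 15 randomised, 15/(1 − s), rounded up | 17 | 19 | 22 | 30 |

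**The case against.** **The outcome is participant acceptability, and a participant questionnaire measures that.** Every consented trial is selected by consent, and the larger trial would also enrol volunteers. This stands as a defence of the questionnaire. It does not defend the Discussion sentence, which draws a conclusion about people with depression.

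**The recruitment log may already hold approaches and refusals.** The article condenses a fuller protocol, and it commits to the CONSORT extension for pilot and feasibility trials. This stands: it cannot be said that such data go unrecorded. But Primary outcome measures does not make them part of acceptability.

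A reader might also infer four stronger points. The document does not support them.
- *Recruitment is captured only from appointment 2, because Table 1 starts its ticks there.* The row describes staff monitoring over the whole trial and is measured by logs. Its ticks run to week 8, long after any individual was recruited, so they do not mark when recruitment is recorded. Refusals also make 15 in 6 months harder to reach, so their effect does enter the target even if their reasons do not.
- *Everyone unwilling has left by appointment 2.* Doses can still be refused. Completion of the intervention is tracked under adherence, with a Table 4 target of two of four enemas, and reasons for withdrawal are documented.
- *Ratings will be favourable whatever the truth.* The week 2 and week 8 ratings follow actual experience of the procedure and could be poor.
- *The target can be met by 15 consents.* Only the Table 1 label points that way. The other places listed in step 6 of the working either separate enrolment from consent or tie the 15 to eligible or allocated participants.

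**Conclusion.** The point holds in a limited form. The acceptability measure, as the article defines and schedules it, describes people who had already agreed to an enema trial. It cannot show whether the route is acceptable to people with depression, so the Discussion claims more than the measure can deliver.

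The size of the gap is unknown, because the article gives neither uptake nor reasons for declining. Under the assumed figures it ranges from nothing (no route-based declines) to 87% against 37% (20 such declines). These figures only illustrate what the questionnaire could miss and do not predict the trial's results. The conclusion rests on one assumption, that the consent form describes the enemas and the four-day attendance.

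The enrolment wording is a minor inconsistency. Read as a whole, the article means 15 eligible, allocated participants.

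**What to change.** 1. In the existing recruitment log, count people given the consent form, those who decline, those who fail screening and those randomised. For declines, record a voluntary reason, with enema or four-day attendance as one category.
2. Report the proportion declining for the route beside the questionnaire, as part of acceptability under Primary outcome measures.
3. In the Discussion, limit the acceptability conclusion to people who consented to an enema trial.
4. As a minor clarification, state in Table 4 that successful enrolment means 15 participants randomised, and bring the Enrolment label in Table 1 into line.

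The cost is a few log fields and some wording. Sample size, visits and procedures do not change. The main downside is that reasons for declining will be incomplete, because giving one is voluntary. The decline-for-route proportion should therefore be shown with the number of decliners who gave no reason. Reasons not asked for at the time cannot be reliably recovered later.
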